### Status of the trial

Recruitment to the study began January 2012 and ended December 2013. Final follow-up data was collected in March 2014 and data analysis is ongoing and expected to be completed by June 2016. The CONSORT diagram (Fig. 1) presents the flow of participants during recruitment, enrollment, and follow-up. Of note, 761 individuals contacted the research office to request additional information about the study. Of those requests, 463 individuals were subsequently not interested once the study was described or were unreachable after multiple attempts. In total, 298 individuals completed the phone screening assessment and 129 were determined to meet study inclusion/exclusion criteria and were invited for the in-person assessment and intervention appointment. Ninety-three individuals attended this in-person appointment and 70 were retained through the 12-week follow-up interview.

**Fig. 1 Fig1:**
[figure not shown]
CONSORT Diagram

The total intent-to-treat sample size was 13 participants fewer than the pre-trial power analyses indicated would be necessary to detect a medium effect size change in suicidal ideation; however, based on power calculations for the full sample, this reduced sample will provide 80 % power to detect differences between the two groups in the medium range (Cohen’s d between 0.5 and 0.6 [28]) and less than adequate power to detect small differences. Additionally, the relatively high rate of retention will still allow us to draw meaningful conclusions from the primary and secondary outcomes of interest.

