### Randomization

A computerized minimization randomization algorithm was used to match participants on three variables that may confound analytic results. These three variables are identified gender, history of suicide attempts, and whether the participant was interested in mental health treatment. Participants were randomized using a 1:1 ratio, such that equal numbers of participants were assigned to each condition. Following completion of the T1 assessment, the therapist entered the participants’ data related to the three potentially confounding variables into the computerized program and participants were randomly allocated to one of the two conditions.

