### Power calculation

A power analysis was conducted prior to the start of the study to provide a guide to sample size requirements. Calculations were based on feasible differences in treatment effect at the three-month follow-up assessment (T4). Based on Cohen’s [28] discussion of effect sizes, the effect size from the pilot study was consulted [13]. The effect size for the decrease in suicidal ideation observed during the pilot study was 0.56, which is considered a medium effect. In order to power the study with a medium effect size for detecting changes in suicidal ideation, the study will require 53 participants per intervention condition, using an independent sample *t*-test between the active and control condition (G*Power) [29].

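### The stated 80% power for d between 0.5 and 0.6 counts all 93 randomised; on the T4 t-test used to set the sample size, the 70 retained give 80% power only at d of about 0.68

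*Protocol article*

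**What the plan says.** The Power calculation section of the protocol article ties the sample size to one visit: "Calculations were based on feasible differences in treatment effect at the three-month follow-up assessment (T4"). It takes a pilot effect on suicidal ideation that "observed during the pilot study was 0.56, which is considered a medium effect", uses an independent-samples t-test, and concludes that "the study will require 53 participants per intervention condition", or 106 in total.

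Status of the trial reports the flow: "Ninety-three individuals attended this in-person appointment and 70 were retained through the 12-week follow-up interview".

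The text after Fig. 1 notes that the intent-to-treat sample fell 13 short of the target (106 − 13 = 93). It then says that, calculated on the full sample, the trial has 80% "power to detect differences between the two groups in the medium range", given as d between 0.5 and 0.6. It adds that "the relatively high rate of retention will still allow us to draw meaningful conclusions" about the primary and secondary outcomes. No power figure is given for the 70.

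The Analyses section names a different method for the continuous outcomes: a hierarchical linear model over the repeated assessments, with condition predicting the growth parameters.

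**The concern.** The power statement and the sample-size calculation do not rest on the same people. The trial was sized on a comparison at T4. The revised statement counts 23 participants (93 − 70) who, according to the preceding section, were not retained to T4. The remark on retention then tells the reader that the loss does little harm, with no calculation behind it.

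Suicidal ideation is a primary outcome. If its result is non-significant, a reader is likely to take it as coming from a trial with 80% power for a medium effect at the visit it was sized on. On the article's own t-test basis, that would be too favourable.

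**Working it through.** **Inputs from the article.** Planning effect d = 0.56, T4 as the time point, independent-samples t-test and 53 per arm (Power calculation). Allocation: "Participants were randomized using a 1:1 ratio" (Randomization). 93 attended and 70 were retained at 12 weeks (Status of the trial). Power of 80% (text after Fig. 1).

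**Assumptions.** Two-sided alpha of 0.05, since neither alpha nor sidedness is stated. The same 80% power for the pre-trial calculation. Arms of 46/47 for the 93 and 35/35 for the 70, since the split by arm is not in the text.

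**Formula.** For arms n1 and n2, the noncentrality is d × √(n1·n2/(n1+n2)). Power is the probability that a noncentral t with n1+n2−2 degrees of freedom exceeds the two-sided 5% critical value in absolute size. The normal approximation to the effect detectable with 80% power is (1.960 + 0.842) × √(2/n) for n per arm.

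**Step 1: reproduce the planned size.** 80% power needs 52 per arm at d = 0.56 and 53 at d = 0.55. With 53 per arm, power at 0.56 is 81.5%. The planned figure reproduces. A one-sided 5% test would need only 41 per arm at 0.56, so two-sided 5% is the better fit.

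**Step 2: reproduce the revised statement, then apply the T4 count.** Loss to T4 is 23/93 = 24.7%.

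| Sample | d at 80% power | Power at 0.50 | Power at 0.56 | Power at 0.60 |
|---|---|---|---|---|
| 93 (46/47) | 0.587 | 66% | 76% | 82% |
| 70 (35/35) | 0.679 | 54% | 64% | 70% |

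Normal-approximation check: 2.802 × √(2/46.5) = 0.581 and 2.802 × √(2/35) = 0.670.

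The figure for 93 lies inside 0.5 to 0.6, so the article's range reproduces for the full sample. The figure for 70 lies outside it.

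**Step 3: sensitivity to the assumptions.** Unequal T4 arms raise the detectable d: 0.680 at 33/37, 0.686 at 30/40 and 0.709 at 25/45. With a one-sided 5% test, the detectable d for 70 is 0.600, the upper edge of the stated range.

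**Step 4: what a repeated-measures model might recover.** This is a range resting on assumptions, not a figure from the article. Assume four assessments, constant within-person correlation ρ, a common baseline mean, and a treatment contrast at T4 (normal approximation). If the 23 contribute baseline only, the detectable d is 0.670 × √(1−ρ²). The lower figure in each range below has them contribute every visit before T4.

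| ρ | d at 80% power, 70 at T4 | d at 80% power, no loss |
|---|---|---|
| 0 | 0.67 | 0.58 |
| 0.3 | 0.63–0.64 | 0.55 |
| 0.5 | 0.57–0.58 | 0.50 |
| 0.7 | 0.46–0.48 | 0.41 |

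The loss raises the detectable effect at every correlation tried. Whether the result falls above, inside or below 0.5 to 0.6 depends on ρ.

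**The case against.** The strongest reply is that no stated number is miscalculated. The article labels its basis as the full sample, 0.587 does lie between 0.5 and 0.6, and the counts of 93 and 70 are both printed just before the power statement. That stands: the loss is disclosed, but it is not carried into the power figure. A reader might infer that 80% power is claimed at every d in the range and so is false over most of it. The more natural reading is that the range locates the detectable effect.

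A reader might also infer that 53 per arm was too few, because d = 0.5 would need 64. The article does not support this. Its aim was "In order to power the study with a medium effect size for detecting changes in suicidal ideation", but the medium effect it names is 0.56, for which 53 is sufficient.

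The second reply is that no T4 t-test is planned as the analysis. The t-test was only the device for setting the sample size, and the hierarchical linear model can use visits that the 23 completed before they were lost. This also stands. It means 0.68 is a benchmark on the sizing basis, not the power of the planned model. It does not rescue the published statement, because the article neither gives a correlation nor claims this gain.

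Third, the text after Fig. 1 names no time point, and the aims cover 1, 4 and 12 weeks. But it measures the shortfall against the pre-trial calculation, which is tied to T4.

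**Conclusion.** The point holds in a limited form. The claim of 80% power for d between 0.5 and 0.6 is right for 93 participants with nobody lost, where the detectable d is 0.59 and power at the planning effect of 0.56 is 76%. It does not hold on the T4 t-test basis with the 70 retained, where the detectable d is 0.68 and power at 0.56 is 64%. These figures assume a two-sided 5% test and a 35/35 split.

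A reader might go further and conclude that the trial's planned analysis is underpowered at T4, or that a null result must be inconclusive. The article supports neither. The power of the hierarchical model depends on a correlation that is not given, and a non-significant result should be judged by what its confidence interval excludes.

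**What to change.** Replace the power statement after Fig. 1 with wording such as:

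> With no loss to follow-up, 93 participants give 80% power for d of about 0.59. On the t-test basis used for sample size, the 70 assessed at T4 give 80% power for d of about 0.68, and 64% power for d = 0.56 (two-sided 5%, equal arms assumed). The planned hierarchical linear model may recover some of this, depending on the within-person correlation.

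Replace the assumed alpha and arm split with the actual ones. If credit is claimed for the hierarchical model, give its power with the assumed correlation and the basis for it.

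Remove the sentence on retention and meaningful conclusions, or qualify it with the 70 of 93 count and the figures above. State that a non-significant suicidal ideation result will be interpreted by its confidence interval.

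The cost is a less favourable stated power. The design, data and planned analysis do not change.

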## Discussion

The importance of studying suicidal individuals who are not engaged in mental health treatment cannot be understated. Recruiting such individuals proved a challenge. Notably, the trial study inclusion criteria initially required that participants be without mental health treatment for one year prior to their enrollment; however, seven months into recruitment, it was determined that this requirement was slowing recruitment efforts and the criteria was modified to no mental health treatment one month prior to enrollment. Given the low rates of contact in the one month prior to suicide reported by Luoma and colleagues [9], we were confident that a non-treatment engaged population was still represented by this eligibility criteria modification. While this change suggests that more work is needed to maximize the effectiveness of outreach to this as-yet out-of-reach group, our success in reaching individuals who were not engaged in treatment suggests that at least some subset of this population is amenable to research and treatment participation. The impact of the results of this randomized controlled trial will provide future researchers with tools and strategies to enhance their own recruitment and outreach efforts as the field continues to develop and evaluate interventions for this high-risk group.

### Ethics approval and consent to participate

In addition to passing the National Institute of Mental Health ethics review (identification number: 1F31MH095257), the study has been approved by the Human Subjects Division of the Institutional Review Board at the University of Washington (application number: 40846). Consent was obtained from each participant prior to collecting any data from them.

### Consent for publication

Not applicable.

### Availability of data and materials

Complete data from this study can be obtained by contacting the first author once data analysis has been completed.

## Abbreviations

DBT: Dialectical behavior therapy
DBT-BSI: Dialectical behavior therapy brief suicide intervention
DSMB: Data and Safety Monitoring Board
RT: Relaxation training
